### The efficacy of the intervention

Preliminary cohort studies report that manual rotation is associated with a reduction in caesarean section and adverse maternal outcomes:In a retrospective cohort study, Schaffer *et al.* (2006) (n = 731) reported that the caesarean section rate was lower in women who had a successful manual rotation compared to when the fetus was unable to be rotated (2% versus 34%) [26]. However, there was no control group of women for whom a manual rotation was not performed and it is not possible to know if this was due to the procedure itself or to underlying confounders such as a smaller fetus.In a prospective cohort study with historical controls (n = 61), the local labour ward policy was changed from not performing prophylactic manual rotation to routinely performing the procedure for OP position about ‘half way’ into the second stage of labour [12]. The operative delivery rate for fetuses in the OP position fell from 73% prior to the change in policy to 23% after the policy was implemented, but this study design is subject to a significant risk of bias.Schaffer *et al*. (2011) re-reported their 2006 data with a control group identified retrospectively from a database and found a 9% risk of caesarean section when manual rotation was performed compared with a 41% risk when it was not [13]. However, the authors had information on the fetal position at the time of birth but not earlier in the second stage of labour when the procedure was performed. Thus OP fetuses that were destined to rotate naturally to the OA position would have been included in the intervention group, but not the control group, which would result in an overestimation of the caesarean section rate in the control group and of the efficacy of manual rotation.

Thus preliminary studies suggest that manual rotation reduces the risk of operative delivery but are susceptible to significant bias. An RCT would best provide unbiased answers regarding the effects of manual rotation of the fetal occiput on maternal and perinatal outcomes.

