### Individuals who will perform the intervention

Only obstetricians or midwives who are experienced in performing a manual rotation and have performed at least 20 procedures will participate in the study. All operators will complete a questionnaire outlining their technique and experience.

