### Randomization/allocation concealment

Randomization will be stratified by parity, hospital site and epidural due to the potentially strong association between operative delivery (the primary outcome) and each of these factors. Randomization will be centrally controlled using computerized sequence generation, which can be accessed 24 hours per day using a toll-free telephone line.

In order to reduce the risk of randomising an ineligible participant, randomisation will occur immediately before the intervention or sham procedure is to be performed. An example of a participant becoming ineligible would be if the fetus rotated from the occiput posterior to occiput transverse position. Each investigator will complete a data collection form at the time the manual rotation or sham procedure is performed outlining the treatment allocation, clinical findings, and whether or not the fetus was successfully rotated.

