### Analysis

Analysis will be by intention-to-treat (according to treatment allocation), including withdrawals and losses to follow-up. Losses to follow-up for the primary outcome are not expected because randomisation will occur at full dilatation and the primary outcome is the mode of delivery.

The results will be reported according to CONSORT guidelines.

Demographics and other potential confounders will be compared by treatment allocation in a univariate analysis. Categorical outcome measures will be compared by proportions (chi-squared test), means for normally distributed data (*t*-test), or rank order for non-normally distributed data (Mann–Whitney-*U* test).

A logistic regression analysis of treatment allocation and other variables on the primary outcome measure, operative delivery, will be performed. The following variables will be considered for the logistic regression model: maternal body mass index, maternal age, maternal height, maternal ethnicity, gestation, induction of labour, gestational diabetes, neonatal gender, and RCOG CTG classification in the second stage of labour. Parity, study site and the presence of epidural for intrapartum analgesia at the time of randomisation will not be included because randomisation is stratified for these variables. Only variables where *P* <0.25 in the univariate regression will be included in the multivariate model. Continuous variables that do not show a linear association with the logit function will be divided into quartiles and treated as categorical. Interaction terms will be considered for treatment allocation versus each of the other variables and where clinically appropriate between non-treatment variables. *P* <0.01 will be considered evidence of interaction. Terms will be excluded from the model in a stepwise backward manner until all remaining terms are both statistically significant (*P* <0.05) and clinically significant (that is, removal of the term results in a clinically significant change in the estimate of the odds ratio of treatment allocation for the primary outcome). The analysis will be performed using SAS 9.2 (or a more recent version of SAS).

Subgroup analyses will be performed according to the technique of manual rotation employed (manual/whole hand versus digital/fingers) and according to operator ability (data will be divided into two approximately equal groups according to the success rate of the operator who performed the manual rotation).

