## Discussion

This trial addresses an important clinical question concerning a commonly used procedure that has the potential to reduce operative delivery and its associated complications. Due to the nature of the intervention, a number of issues are worthy of discussion.

First, empirical evidence suggests that blinding reduces bias in randomised controlled trials. However, blinding may be difficult in the case of procedural interventions. In this trial, we intend to assess the efficacy of blinding by asking the woman’s carer to guess the treatment allocation after manual rotation or sham rotation has occurred. The purpose of this is to allow the reader to assess the risk of bias associated with knowledge of treatment allocation.

Second, the efficacy of procedural interventions may depend on the experience and training of individual operators. The ‘success’ of manual rotation of individual operators will be assessed by recording the ultrasound determined fetal position after the manual rotation or sham procedure has been performed. We will report on any major differences between the success rates of individual practitioners.

Third, due to the ethics of consent in labour, consent will be obtained when it is unknown if the fetus will be in the occiput posterior position in the second stage of labour, which is an eligibility criterion. Thus, it is likely that only a minority of consented participants will be randomised, which will result in a large workload per randomisation (the pilot study was used as a reference).

Finally, women who progress rapidly in labour may give birth before they can be randomised and women with regional analgesia will have more opportunity to be consented. This could result in the study population having a higher background risk of the primary outcome than non-consented women who meet our eligibility criteria, which could impact the generalisability of our findings.

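### Splitting operators by the rotation success seen in the trial biases the ability subgroup towards a larger benefit in 'able' hands, if success is linked to mode of delivery

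*Protocol article*

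**What the plan says.** The Analysis section of the protocol article plans two subgroup analyses, one by technique and one by operator ability. For the second, "data will be divided into two approximately equal groups according to the success rate of the operator who performed the manual rotation".

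Two other sections show where the success rate comes from. The Discussion says that each operator's success "will be assessed by recording the ultrasound determined fetal position after the manual rotation or sham procedure has been performed". The section on randomisation and allocation concealment has the investigator complete a form at the time of the procedure "outlining the treatment allocation, clinical findings, and whether or not the fetus was successfully rotated". No success rate from before the trial is named as the classifier.

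Two further statements bear on the point. "All operators will complete a questionnaire outlining their technique and experience", and each must have done at least 20 procedures (Individuals who will perform the intervention). Operator is not a stratification factor: "Randomization will be stratified by parity, hospital site and epidural".

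**The concern.** A subgroup variable should be fixed before randomisation, or at least be unaffected by what happens afterwards. Here it is built from the result of the procedure in the rotation arm. In a rotated woman, success lies between the procedure and her mode of delivery. If an operator's few rotated women happen to be easy to rotate, that operator is ranked as able, and the same women contribute a low operative-delivery rate to the 'able' half. The operator's sham women gain nothing from that luck. The difference between arms is therefore pushed up in the high-success half and down in the low-success half.

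The article raises the same doubt about a cited retrospective cohort, where caesarean section followed 2% of successful and 34% of unsuccessful rotations: "it is not possible to know if this was due to the procedure itself or to underlying confounders such as a smaller fetus".

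At stake is the reading of this one subgroup. It could suggest that rotation works mainly in skilled hands when skill made no difference. If operators do differ in skill, the bias is added to the real difference and the analysis cannot separate the two.

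**Working it through.** **Inputs from the article.** 127 women per arm; operative delivery 68% (control) and 50% (intervention); two-sided alpha 0.05; power 80% (Sample size); 1:1 allocation (Trial design).

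**The plan's own figure.** With p̄ = 0.59 and d = 0.18:

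n = [1.960·√(2·0.59·0.41) + 0.842·√(0.68·0.32 + 0.50·0.50)]² / 0.18² = (1.363 + 0.576)² / 0.0324 ≈ 116.0, or 117 per arm after rounding up.

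With the continuity correction, (116.0/4)·[1 + √(1 + 4/(116.0·0.18))]² ≈ 126.9, which rounds up to 127. The stated 127 per group reproduces.

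**Assumptions, not in the article.** The number of operators K; a true success probability of 70% for every operator; and these operative-delivery rates after successful and failed rotation:
- A, milder link: 42.3% and 68% (0.7·42.3 + 0.3·68 ≈ 50)
- B, stronger link: 36% and 82.7% (0.7·36 + 0.3·82.7 ≈ 50)
- C, no treatment effect but success prognostic: 60% and 86.7% (0.7·60 + 0.3·86.7 ≈ 68)
- D, success unrelated to outcome: 68% and 68%

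**Method.** 3,000 simulated trials per scenario. Identical operators are assigned at random to women in both arms and ranked by observed success in their rotated women. The data are split into two roughly equal halves, with sham women following the operator who did the sham. The high-minus-low difference in risk difference gets a Wald test. The true value is zero throughout.

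| Operators | A: gap (points), rejection at 5% | B | C |
|---|---|---|---|
| 4 | -2.8, 5.1% | -5.2, 7.2% | -2.6, 5.3% |
| 10 | -5.0, 6.9% | -8.6, 10.8% | -4.8, 6.5% |
| 20 | -7.1, 8.8% | -12.8, 18.5% | -7.6, 10.1% |
| 40 | -10.3, 13.6% | -18.2, 31.6% | -10.8, 14.3% |

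Under D the gap is about 0 and rejection about 5%.

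**Why the figures scale this way.** The false gap is the chance difference in success between the halves times the difference in outcome between failure and success. Dividing recovers the first factor. For K = 20, 7.1/25.7 and 12.8/46.7 both give about 0.27 to 0.28; for K = 4, 2.8/25.7 and 5.2/46.7 both give about 0.11. So a reader can apply another link. With 35% and 85% (50 points) and 20 operators, 0.276·50 ≈ 13.8 points, which agrees with direct simulation (-13.8, 21% rejection at 5%). With a 32-point link (40.4% and 72.4%), matching the size of the caesarean gap in the cited cohort, simulation gives 3.3 points with 4 operators, 5.2 with 8 and 9.1 with 20, with rejection at 5% of 5.4%, 6.4% and 11.2%.

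**Stricter threshold.** At a 1% test with 20 operators, rejection is about 3% with the milder links and about 8% with 35%/85%.

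**Same trials, classifier from outside the trial.** With operators ranked on 20 simulated earlier procedures each, the gap lies between -0.6 and +0.4 points in every scenario and rejection between 4.5% and 6.3%.

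**The case against.** The strongest objection concerns size. Nothing in the article fixes the number of operators, and it hints that they are scarce. Each needs at least 20 procedures, while only 38% of surveyed obstetricians had done a rotation in the past year, most of them one or two (The intervention in current practice). With about 4 operators the bias is small and the test is close to its nominal level. Against that, the trial is multicentre and each centre must offer a 24-hour service with experienced operators, so a very small number cannot be assumed either. The objection stands as a limit on size, not on direction.

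The 5% interaction test is also a choice made for this check. The only interaction threshold in the Analysis section is 1%, stated for the regression model, and no test is stated for the subgroup. At 1% the false-positive rates are much lower, though still above nominal with 20 operators.

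A reader might go further and infer three things that the article does not support:
- **That the rule must produce a false effect.** It does so only if success is linked to operative delivery. The one link shown is for caesarean section in a cohort.
- **That leaving unstated where sham women go is a separate error.** This is detail that an article may leave to the analysis plan. The same investigator does either procedure, so classifying sham women by their operator is the natural reading.
- **That the subgroup exists to guide training.** The Discussion says only that efficacy may depend on experience and training, and that major differences in operators' success rates will be reported.

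**Conclusion.** The concern holds for the operator-ability subgroup. The classifier comes from post-randomisation results in the same rotated women whose deliveries are compared, and the direction of the bias is predictable. Its size is conditional. Assuming 70% success for every operator, 127 per arm and 68% versus 50%, and across the milder and stronger links, the false gap is:
- about 3 to 6 points with 4 operators (about 5% to 7% rejection at 5%)
- 4.5 to 8 points with 8 operators
- 7 to 14 points with 20 operators (9% to 21% rejection at 5%, about 3% to 8% at 1%)
- none if success is unrelated to outcome

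A reader might take this as a doubt about the main result. It is not: the primary intention-to-treat comparison and the sample size are untouched. The point is worth correcting because the article itself fixes the classifier, and a better-founded one is already being collected.

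**What to change.** Define operator ability from information fixed before randomisation, such as the number of previous rotations reported in the operator questionnaire, with the cut-point set in advance. Classify women in both arms by the operator who did the rotation or the sham. Report the treatment-by-group interaction with a confidence interval.

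If in-trial success is still shown, label that analysis descriptive and do not take it as evidence of an ability effect. Limiting it to the rotation arm does not help: the selection stays and the randomised comparison is lost. Nor should success be recomputed leaving out the woman being classified. Removing her own result moves successes towards the low group and failures towards the high group, so the bias reverses. With 4 operators and the 35%/85% link, simulations gave a reverse gap of about 5 points and rejection of 16% to 19% at a nominal 5%.

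The cost is a change of analysis wording, since the questionnaire already exists. The downside is real: every operator has at least 20 procedures, so reported experience is range-restricted and a coarser measure of skill than observed success.

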### Data safety monitoring committee

Draft terms of reference for a data and safety monitoring committee provide for potential cessation of the trial if significant safety concerns are raised. The data and safety monitoring committee will consist of three people who are not involved in the study and do not have a working relationship with the primary investigators. Adverse events will be reported to the committee.

### Interim analysis and stopping rules

There will be no interim analysis. The Data Safety Monitoring Committee may advise that the trial be stopped if significant concerns about the safety of manual rotation are found.

### Harm

Any serious complications will be referred to the Data Monitoring Committee.

### Auditing

There will be no external auditing of the trial.

### Research ethics approval

This study has been approved by the Ethics Review Committee (RPAH Zone) of the Sydney Local Health District, Sydney, Australia, Protocol number X110410.

## Discussion

This trial addresses an important clinical question concerning a commonly used procedure that has the potential to reduce operative delivery and its associated complications. Due to the nature of the intervention, a number of issues are worthy of discussion.

First, empirical evidence suggests that blinding reduces bias in randomised controlled trials. However, blinding may be difficult in the case of procedural interventions. In this trial, we intend to assess the efficacy of blinding by asking the woman’s carer to guess the treatment allocation after manual rotation or sham rotation has occurred. The purpose of this is to allow the reader to assess the risk of bias associated with knowledge of treatment allocation.

Second, the efficacy of procedural interventions may depend on the experience and training of individual operators. The ‘success’ of manual rotation of individual operators will be assessed by recording the ultrasound determined fetal position after the manual rotation or sham procedure has been performed. We will report on any major differences between the success rates of individual practitioners.

Third, due to the ethics of consent in labour, consent will be obtained when it is unknown if the fetus will be in the occiput posterior position in the second stage of labour, which is an eligibility criterion. Thus, it is likely that only a minority of consented participants will be randomised, which will result in a large workload per randomisation (the pilot study was used as a reference).

Finally, women who progress rapidly in labour may give birth before they can be randomised and women with regional analgesia will have more opportunity to be consented. This could result in the study population having a higher background risk of the primary outcome than non-consented women who meet our eligibility criteria, which could impact the generalisability of our findings.

### Protocol amendments

If modification to the study protocol is considered necessary, then permission will be sought from the ethics committee and the changes will be described in the final report.

### Confidentiality

All the information collected from the study will be treated confidentially, and only the researchers will have access to it. Hard copies of data collection forms will be stored in a locked office. The electronic database will be de-identified and stored at a different location to codes linking identifying data to study identification numbers. The electronic database will be on Microsoft Access, password-protected, and only accessible by research staff.

### Site investigators

In each participating centre, a lead investigator (obstetrician) will be responsible for identification, recruitment data collection and completion of relevant trial forms, along with adherence with study protocol. Each lead investigator will be a steering committee member.

### Data manager

The data manager will be responsible for maintenance of the trial IT system, data entry and data verification.

### Trial status

Start date: 16 April 2012.

Number currently recruited: 160.

## Abbreviations

ARM: artificial rupture of membranes
CS: caesarean section
NSW: New South Wales
NICU: neonatal intensive care unit
OA: occiput anterior
OP: occiput posterior
OT: occiput transverse
PPH: postpartum haemorrhage
RCT: randomised controlled trial
